#### 4.4.11 Data extracted from patient hospital records

Patient data including age, sex, cancer site, diagnosis, treatment, current medications will be extracted from the patient records exclusive of patient identifiers from The Orchid Centre database located in Cork University Hospital using the Nurse Record Form. All survivorship services that were provided by the CUH and used during the 12 month period will be extracted from the patient records.

## 5.0 Study Calendar

### 5.1 Intervention Arm

| Actions and Instruments b                                                                                                                                                                                                                                                                                                                                                                                               | Baseline a
(Months)
→ | 2 | 4 | 6 | 8 | 10 | 12 |
|------------------------------------------------------------------------------------------------------------------------------------------------------------------------------------------------------------------------------------------------------------------------------------------------------------------------------------------------------------------------------------------------------------------------------------|----------------------------------------|---|---|---|---|----|----|
| Information provided; recruit to study; consent form; GDPR Data form, visit to survivorship clinic, meet dietician- dietetics assessment (e.g. BMI, diet)
Baseline: patient clinical and socio-demographics collected                                                                                                                                                                                                           | X                                      |   |   |   |   |    |    |
| Randomisation                                                                                                                                                                                                                                                                                                                                                                                                                      | X                                      |   |   |   |   |    |    |
| Current medications                                                                                                                                                                                                                                                                                                                                                                                                                | X                                      | X | X | X | X | X  | X  |
| Comorbidities                                                                                                                                                                                                                                                                                                                                                                                                                      | X                                      | X | X | X | X | X  | X  |
| ePRO Health related-Quality of Life survey. Instruments used as follows:
1. EORTC-QLQ-C30 (30 items)
2. Considering patients cancer type:
• Cervical cancer: EORTC QLQ – CX24 (24 items)
• Endometrial cancer: EORTC QLQ – EN24 (24 items)
• Breast cancer: EORTC QLQ - BR23 (23 items)
3. EQ-5D-5L (5 items) (measures QALY)
4. Appraisal Self-Care Agency-R (15 items) (measures power to self-care) | X                                      |   |   |   |   |    | X  |
| ePRO Patient-reported symptom questionnaire includes PROMIS and PRO-CTCAE items
Fear of cancer recurrence, Adherence                                                                                                                                                                                                                                                                                                            | X                                      | X | X | X | X | X  | X  |
| Body weight                                                                                                                                                                                                                                                                                                                                                                                                                        | X                                      | x | x | x | x | x  | X  |
| BIA measurement                                                                                                                                                                                                                                                                                                                                                                                                                    | X                                      |   |   |   |   |    | X  |
| Hand grip strength                                                                                                                                                                                                                                                                                                                                                                                                                 | X                                      |   |   |   |   |    | X  |
| Diet intake assessments (multiple 24hour dietary recalls & food frequency questionnaire)                                                                                                                                                                                                                                                                                                                                           | x                                      |   |   |   |   |    | X  |
| Diet quality assessment
(World Cancer Research Fund / American Institute for Cancer research score)                                                                                                                                                                                                                                                                                                                             | x                                      |   |   |   |   |    | X  |
| World Cancer Research Fund/American Institute for Cancer Research (WCRF/AICR) score                                                                                                                                                                                                                                                                                                                                                | X                                      |   |   |   |   |    | X  |
| Diet Education                                                                                                                                                                                                                                                                                                                                                                                                                     | x                                      |   |   |   |   |    |    |
| Personalised nutrition counselling if identified at nutritional risk c                                                                                                                                                                                                                                                                                                                                                  | x                                      |   |   |   |   |    |    |
| Use of resources form                                                                                                                                                                                                                                                                                                                                                                                                              |                                        |   |   | X |   |    | X  |
| Follow up phone call by clinic nurse                                                                                                                                                                                                                                                                                                                                                                                               |                                        |   |   | X |   |    |    |
| End of study patient questionnaire—includes system usability, satisfaction scales                                                                                                                                                                                                                                                                                                                                                  |                                        |   |   |   |   |    | X  |
| Qualitative interviews with patients, healthcare professionals and wider team, stakeholders (process evaluation)                                                                                                                                                                                                                                                                                                                   |                                        |   |   |   |   |    | X  |
| Clinician record of actions/follow-up at survivorship and symptom management encounters
Data extracted from hospital records                                                                                                                                                                                                                                                                                                    |                                        | X | X | X | X | X  | X  |
| Drop out date, reason (data collected as required)                                                                                                                                                                                                                                                                                                                                                                                 |                                        |   |   |   |   |    |    |

- a. Baseline measures may be completed up to 2 weeks after enrollment and prior to attendance at the initial clinic visit. For patients who do not complete the baseline measures, the date for the follow-up measures will be determined using the enrollment date (i.e. 2, 4, 6, 8, 10, 12 months from the date of enrollment)

- b. The every 2 month measures may be completed up to two weeks after each survey becomes available. Electronic survey reminders will be sent to patients to facilitate ePRO completion. Dates for all follow-up measures will be based on the enrollment date.
- c. Repeat dietetic collections if referred to dietitian from diet trigger questions and/or if remain on dietitian caseload from baseline interview. This will be based on individual needs.

Note: Clinical follow-up will be according to standard of care. Follow-up visits are not specifically required per protocol other than those needed for routine clinical care.

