### 2.3. Secondary Objectives:

- To describe the symptoms experienced by patients with breast and gynaecologic cancers and evaluate the impact of the intervention on select reported symptoms over a 12-month period.
- To evaluate the impact of the survivorship clinic on quality of life using serial ePRO measures.
- To explore self-care agency and its relationship to quality of life and symptoms experienced in both arms.
- To evaluate adjuvant endocrine therapy medication adherence rates at 12 months after study entry in both arms, and factors associated with non-adherence in early-stage HR-positive breast cancer patients.
- To explore and assess the satisfaction of patient and Health Care Professionals with the intervention and to determine their perceptions of the systems usability.
- To estimate the resource use and economic impact of a women's malignancy survivorship clinic.
- To evaluate the impact of a dietetic intervention by assessing changes in dietary intake and diet quality over a 12-month period.
- To evaluate the impact of a dietetic intervention on body weight, lean body mass, fat mass, muscle strength and nutritional risk over a 12-month period.

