#### **4.4.9 Discontinuation of Subjects**

All patients who initiate the study will be included in the overall analysis. All reasons for discontinuation of participation in the trial will be documented clearly in the trial record.

The reasons for discontinuation may include:

- a) At subject's own request.  
*Note: The reason for discontinuation from the study must be documented.*
- b) Death.
- c) Intercurrent illness or condition that would, in the judgment of the principal investigator, affect assessment of clinical status to a significant degree.
- d) Evidence of disease recurrence during study.
- e) Study is terminated for any reason.
- f) Subject withdraws consent for follow-up.
- g) Subject does not complete 2 consecutive ePRO surveys. In that case, the patient will be given the option to continue receiving surveys or to withdraw from the study.

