#### 4.4.10 Usability and Satisfaction

In order to gather information on usability and satisfaction with the computerized questionnaire system, the opinions of patients will be gathered using a modified five-item Usability Survey and four item Satisfaction Survey (Lewis, 1995 and Sharma et al, 2016). The questions in this index are designed to assess different domains of usability of the web-based system, including usefulness, ease of use and satisfaction with use, and were adapted from a previously developed computer usability and satisfaction questionnaire. The survey will also include some open-ended questions allowing participants to share their perspectives more freely.

As part of the process evaluation, all patients, health care professionals and the broader team involved in the development and implementation of the clinic will be invited to attend either a focus group or one to one interview that will take place after the completion of their involvement in the study (in person or remotely). Attendees will be asked about their experiences of the survivorship clinic and associated processes, limitations, challenges and possible benefits and future possibilities concerning the intervention. The interview will be audio-recorded with the consent of participants (both patients and HCPs), and will last approximately one hour. Transcribed audio will be analysed using qualitative content analysis. A priori it is anticipated that we will interview up to twenty patients, ten members of the MDT and ten broader team/stakeholders/service providers. A lesser number may be required if data saturation is attained earlier.

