| Clinician/stakeholder questionnaires                                                                                                                                                                                                                                                                                                                                                                                                 |                       | X         |
| Qualitative interviews with patients, healthcare professionals and wider team
(process evaluation)                                                                                                                                                                                                                                                                                                                                |                       | X         |
| Clinician record of actions/follow-up at survivorship and symptom management encounters
Data extracted from hospital records                                                                                                                                                                                                                                                                                                      |                       | X         |
| Drop out date, reason (data collected as required)                                                                                                                                                                                                                                                                                                                                                                                   |                       |           |

- a. Baseline measures may be completed up to 2 weeks after enrollment and prior to attendance at the initial clinic visit. Electronic survey reminders will be sent to patients to facilitate ePRO completion

Note: Clinical follow-up will be according to standard of care. Follow-up visits are not specifically required per protocol other than those needed for routine clinical care.

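### The usability and satisfaction scales are given only at month 12, with none at early exit, so the scores will over-represent patients who kept using the system

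*Protocol*

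**What the plan says.** Section 2.3 sets a secondary objective: "To explore and assess the satisfaction of patient and Health Care Professionals with the intervention and to determine their perceptions of the systems usability".

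Section 4.4.10 names the scaled instruments and who answers them: "the opinions of patients will be gathered using a modified five-item Usability Survey and four item Satisfaction Survey". Some open-ended questions are added. The same section adds a qualitative strand, in which "all patients, health care professionals and the broader team involved in the development and implementation of the clinic will be invited to attend" a focus group or a one-to-one interview "that will take place after the completion of their involvement in the study". It expects up to twenty patients, ten members of the multidisciplinary team and ten from the broader team.

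In the calendar for the intervention arm (5.1), the row "End of study patient questionnaire—includes system usability, satisfaction scales" has a single mark, at month 12. The control calendar (5.2) has the same row, also at 12 months only. Neither calendar nor 4.4.10 mentions giving the questionnaire to a patient who leaves before then. For such patients the calendars list the date and reason of drop-out, and section 6.0 says that reasons will come from Drop Out Forms and from discussions with clinic staff.

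Section 4.4.9 (g) lists among the reasons for discontinuation: "Subject does not complete 2 consecutive ePRO surveys". The patient is then offered the choice of carrying on or withdrawing.

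Separately, the control calendar has a row "Clinician/stakeholder questionnaires" at 12 months. The intervention calendar has no such row.

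**The concern.** A score for a computerised symptom system should reflect everyone who was asked to use it. Here the people most likely to have found it burdensome are also the most likely to be gone when the questionnaire is sent, and one listed exit route is defined by not using the system. The missing ratings are therefore unlikely to be a random subset.

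This is a matter of data collection, not of analysis. Whatever an analysis plan says about missing data, it cannot recover scores that were never requested, and a stated reason for leaving does not stand in for a usability or satisfaction rating.

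At stake is how the study is used. Section 2.1 says that, if the intervention proves feasible, it will be offered to all patients as standard care. Acceptability ratings taken only from those still taking part at month 12 are weak support for that step.

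**Working it through.** **Stated figure.** The protocol gives no expected satisfaction rate, no drop-out rate and no threshold for satisfaction, so there is none to reproduce. The check compares the sections and then illustrates the possible size.

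**Step 1: what is collected from whom.**

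| Source | Patient reaching month 12 | Patient stopping earlier |
|---|---|---|
| Usability and satisfaction scales (4.4.10; 5.1, 5.2) | Yes | Not scheduled |
| Drop-out date and reason (5.1, 5.2, 6.0) | Not applicable | Yes, reason only |
| Interview or focus group (4.4.10) | Invited | Invited, but up to twenty patients in all and no quota for leavers |

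**Step 2: where the exit rule bites.** Intervention patients receive surveys at baseline and months 2, 4, 6, 8, 10 and 12, so two consecutive misses can occur well before month 12. Controls are surveyed only at baseline and month 12, so for them two consecutive misses would have to include month 12 itself. Before month 12 this route therefore acts only in the intervention arm, the arm whose experience the objective is about.

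**Step 3: size, as an illustration.** Let *d* be the share stopping before month 12, *p* the satisfied proportion among completers and *q* that among leavers.

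- Proportion among all patients = *p*(1 − *d*) + *qd*
- Overstatement by the completers' figure = *d*(*p* − *q*)
- Limits with nothing assumed about leavers: *p*(1 − *d*) to *p*(1 − *d*) + *d*

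Assumed, with no source in the protocol: *p* = 85%, *d* = 10% or 20%, *q* = 40% or 60%.

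| *d* | *q* | All patients | Overstatement |
|---|---|---|---|
| 10% | 60% | 0.9 × 85 + 0.1 × 60 = 82.5% | 2.5 points |
| 10% | 40% | 0.9 × 85 + 0.1 × 40 = 80.5% | 4.5 points |
| 20% | 60% | 0.8 × 85 + 0.2 × 60 = 80.0% | 5.0 points |
| 20% | 40% | 0.8 × 85 + 0.2 × 40 = 76.0% | 9.0 points |

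With no assumption about leavers, the limits are 76.5% to 86.5% at *d* = 10% and 68.0% to 88.0% at *d* = 20%. If leavers were as satisfied as completers, the overstatement would be zero.

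**Step 4: the clinician questionnaire.** Section 2.3 wants the views of health care professionals. Section 4.4.10 obtains them by interview or focus group and describes no questionnaire for them. Section 5.2 lists one; 5.1 does not. The three places disagree on whether it exists and where it belongs.

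**The case against.** The best defence is that leavers are not silenced. The interview invitation goes to all patients once their own involvement ends, whether or not they reached month 12, and asks about limitations and challenges. Missing two surveys does not by itself end participation, since the patient may choose to continue. The objective is partly exploratory, which interviews serve. Some leavers could never be asked, because they have died or withdrawn consent for follow-up, and those who can be asked may respond poorly, so an exit questionnaire would remove only part of the bias. All of this stands, and it rules out saying that patients who stop can never give a view. It does not close the gap in the scales: interviews with up to twenty patients, and no places set aside for leavers, yield no score that can be put beside the completers' scores.

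Two stronger readings are tempting, and the protocol supports neither.

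- A reader might infer that the objective is answered by the wrong people. It is not: intervention patients do complete the scales, interviews with professionals appear in both calendars, and professionals are not randomised. The place of a row in a patient-arm calendar therefore does not decide which clinicians answer or what they rate.
- A reader might infer that control scores dilute the result. Section 4.4.10 says the survey concerns the computerised questionnaire system, which controls also use, and nowhere says that the arms will be pooled. Reporting by arm can be left to the analysis plan.

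**Conclusion.** The point holds for the scales. As scheduled, usability and satisfaction scores come only from patients still participating at month 12, and in the intervention arm disengagement from the system is one of the ways to drop out of that group. The direction of the bias is favourable to the system if leavers are less satisfied than completers, which is plausible but not shown. Its size cannot be known from the protocol; 2.5 to 9 points is an illustration on assumed rates.

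This affects one secondary objective with no decision rule attached, so it is a worthwhile and inexpensive improvement rather than a threat to the trial. The clinician questionnaire row is a minor inconsistency to be reconciled.

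**What to change.** 1. In 5.1 and 5.2, mark the patient usability and satisfaction questionnaire as due at month 12 or at discontinuation, whichever is first. Offer it with the Drop Out Form, except after death or withdrawal of consent for follow-up.
2. State in 4.4.10 that the number answering will be reported over the number randomised, by arm, with completers and discontinued patients shown separately.
3. Reconcile 5.1, 5.2 and 4.4.10 on the clinician and stakeholder questionnaire. Either describe it in 4.4.10 and list it in 5.1, or delete the row from 5.2 and state that the satisfaction of health care professionals is assessed by interview or focus group.

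The cost is calendar wording and one additional sending of a survey that already exists. The drawbacks are a probably low response among those who leave and possibly a less favourable satisfaction figure. Showing respondents over randomised patients makes any remaining gap visible.
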